
### Clinical study endpoints

The primary endpoint is defined by a blinded independent centralized revue of progression-free survival. cPFS is defined as the time from randomization until progression or death; patients alive and without documented progression at last follow-up news have PFS censored at this date or at initiation of new anticancer treatment (if applicable). Progression will be assessed by a blinded independent centralized review of CT-scan per RECIST criteria 1.1.

#### Secondary endpoints are:

Progression-Free Survival (local PFS) is defined as the time from randomization until progression or deaths; patients alive and without progression at last follow-up news are censored at this date.OS defined by the delay between randomization and the occurrence of death due to any cause. Patients still alive at the time of analysis (including lost of follow-up) will be censored at the last known alive date.Safety will be assessed by the toxicity grading of the National Cancer Institute Common Terminology Criteria for Adverse Events (NCI-CTCAE v 5.0). To be considered evaluable for safety, patients must have received at least one treatment dose.Quality of life (QL) will be assessed by the European Organization for Research and Treatment of Cancer (EORTC) core QL questionnaires, the EORTC QLQ-C30 and QLQ-OES18 (Oesophageal Cancer Module).

### Medical procedures

FOLFOX 4 simplified protocol, 1 infusion every 2 weeks during 3 months starting with radiotherapy (± 1 day): IV oxaliplatin 85 mg/m2 in 2 h on day 1 (D1), IV Leucovorin 200 mg/m2 in 2 h on day 1 (D1), followed by IV 5-FU 400 mg/m2 in 10 min on day 1 (D1) followed by IV continuous infusion 5-FU 2400 mg/m2 during 46 h.

Premedications use: Anti-emetic premedication and Hematopoietic growth factor will be administered according to local standards of care.Durvalumab is delivered to patients included in the experimental arm with a cumulative dose over the whole trial of 18,000 mg (12 cycles):◦Every 4 weeks during concurrent RT and FOLFOX (dose: 1500 mg): 3 infusions (IV administration before the FOLFOX regimen).◦Every 4 weeks (dose: 1500 mg) after FOLFOX completion: 9 infusions (IV administration).

### Treatment planning

Radiotherapy will be delivered with FOLFOX with or without durvalumab (depending on randomization) and procedure will be the same for all treated patients randomized in both arms. If feasible, radiotherapy will ideally be delivered after oxaliplatin infusion infusion the days of chemotherapy.

Target volumes are delineated according to standard procedures [17]. Definitive intensity-modulated radiotherapy or helical tomotherapy will be delivered according to boost integrated technique using high-energy photon (≥ 6 MV) medical linear accelerators (linacs) equipped with a multileaf collimator, Volumetric Modulated Arc Therapy (VMAT) or helical Tomotherapy® during 5 weeks, 5 days per week at a dose of:50 Gray (Gy) in 25 fractions of 2 Gy delivered to the macroscopic disease (tumour and involved lymph nodes)45 Gy in 25 fractions of 1.8 Gy to the adjacent peri-tumoural mucosis and prophylactic lymph nodes.

### Quality assurance in radiotherapy

A Quality Assurance (QA) committee for radiotherapy has been implemented for this trial and composed by the coordinating investigators and UNICANCER team, before starting radiotherapy.

For the RT Quality Review, a dedicated database was set up for the study by Aquilab® Company. The quality assurance program for radiotherapy follows the control steps defined by the Quality Assurance Committee (QA committee) provided in the protocol. Each participating center downloads on the database planning and contouring information for all included patients as soon as these data are available. A prospective review is done by the QA Committee, for every first included patient in each participating center and then every 1 patient out of 5 according to a centralized random selection. The RT quality review will take place within 3 working days after download. For the patients concerned, RT planning is validated by the QA Committee before starting treatment. This prospective planning treatment review will provide a statement about the acceptability of the plans and treatment delivery in terms of delineation, dose constraints, and treatment workflow in accordance with the protocol recommendations and will ascertain the absence of any major protocol deviations.

#### Data management

The randomization in each treatment arm will be performed via the UNICANCER data center located in Institut Régional du Cancer de Montpellier – Val d’Aurelle (ICM) Biometrics unit.

All data necessary to the allocation of the treatment arm must be entered timeliness into the study’s case report forms (CRFs). CRFs will be completed by the investigator and other designated members duly designated from his/her staff and will be controlled and validated according to the standard procedures (included those in the software and the sponsor’s quality assurance procedures). When using the eCRF, traceability of access and changes made to the eCRF are traced by the software (audit trail). At the end of the study and once all the eCRF data are validated, the investigator will login to the eCRF to sign all the pages to validate the data entered for each patient.

Each user has received in his personal mailbox an access code (login) and a personal password automatically generated from the plateform to connect to the eCRF. A password non-disclosure certificate is signed by the principal investigator engaging his/her responsibility regarding the confidentiality of the access codes for all users of the eCRF in his/her centre.

To ensure the authenticity and credibility of data in accordance with the “Décision portant sur les Bonnes Pratiques Cliniques, 24 November 2006”, the sponsor establishes a system of quality assurance that consists in:

The management and the monitoring of the study according to UNICANCER procedures;The quality control data of the investigational centers by the monitor involves:verifying that the protocol, as well as the current guidelines ICH-GCP, the national regulatory requirements, are accurately followed,verifying the informed consent and the eligibility of each patient participating in another research,verifying that the CRF data is consistent and in agreement with the source documents,verifying the notification of each SAE,verifying the drug traceability (dispatching, storage and accountability),verifying that patients are not already participating in another research trial which may exclude their inclusion in this protocol. The monitor also verifies that patients have not participate in another trial following which an exclusion period if applicable before they can participate in another protocol,The audit of the participating investigational centers when deemed necessary;

The monitors and CRAs in charge of trial monitoring will be mandated by the sponsor. They must have access to all patient data as necessary for their duty in accordance with the national regulatory requirements. The monitors and CRAs are bound by professional secrecy under the national regulatory requirements. Written reports must be issued to ensure monitoring visit traceability. In order to ensure the optimal research quality control, the investigator commits to provide the monitor with direct access to all patient files.

Continuous variables will be summarized by arm, using median, minimum, maximum and number of available observations. Qualitative variables will be summarized by arm using: counts, percents, number of missing data. Primary endpoint will be analyzed on the ITT population when the required number of events has been reached.

All randomized patients signed a written informed consent form. Patient information and informed consent from the patient must be handled in accordance with the “French regulation, especially article L.1122–1 and subsequent articles.

The first patient was enrolled in May 2019 and eighteen centers from the PRODIGE Group are participating. To date, 86 out of 120 patients are already enrolled.

#### Treatment tolerance

Safety is monitored on adverse event (AE) occurrence, the use of concomitant treatments, changes occurring in the course of treatment, observed during physical examination and biological examinations (biochemistry, hematology). Severity is determined according to NCI-CTCAE v5.0.

All AEs that occur from the time of the signing of the informed consent form until 150 days after the last dose of durvalumab, whichever is longer, must be reported by the investigator. All AEs will be recorded on the AE page of the eCRF and in the subject’s source documents.

Deterioration as compared to baseline in protocol-mandated laboratory values and vital signs should only be reported as AEs if the investigator considers the event clinically significant or if they fulfil any of the SAE criteria or are the reason for discontinuation of treatment with the IPs.

If deterioration in a laboratory value or vital sign is associated with clinical signs and symptoms, the sign or symptom will be reported as an AE and the associated laboratory result or vital sign will be considered as additional information. Whenever possible, the reporting Investigator should use the clinical rather than the laboratory term (e.g., anemia versus low hemoglobin value). In the absence of clinical signs or symptoms, clinically relevant deteriorations in non-mandated parameters should be reported as AEs.

Deterioration of a laboratory value that is unequivocally due to disease progression should not be reported as an AE/SAE.

Any new or aggravated clinically relevant abnormal medical finding at a physical examination as compared with the baseline assessment will be reported as an AE. The investigator ensures that adequate medical care is provided to the patient. Treatment of the event may require decoding of the investigational medicinal product.

The investigator must immediately following knowledge of the event, notifies the UNICANCER pharmacovigilance unit of any SAE or any new event defined above, whether or not related to the research, which occurs during the ‘trial reporting period’. This reporting period:

Starts at the date of the signature on the informed consent form,Covers the entire period during which the patient is receiving the investigational treatment or is subject to specific procedures related to the trial,Covers a period of 150 days after the last administration of durvalumab for Arm A and 30 days after FOLFOX for Arm B.

Any later SAE, i.e. occurring after a period of 150 days, which is considered to be related to the experimental treatment(s) or to the research (other treatment used, diagnostic procedures and examinations carried out during the research) must be reported without any limitation in terms of deadline.

Notification must be carried out immediately to the UNICANCER pharmacovigilance unit by sending the form “notification of a SAE”, located in the Investigator Master File, completed as precisely as possible, dated and signed by the physician-investigator.

Abnormal laboratory results should be reported as SAE if they possibly put at risk the patient or they require medical intervention to prevent an outcome corresponding to one of severity criteria.

Second cancer, whether or not related to the research, must be reported to the UNICANCER pharmacovigilance unit without any limitation in terms of deadline.

The investigator shall send additional information to the UNICANCER pharmacovigilance unit using a SAE declaration form. All pregnancies and outcomes of pregnancy should be reported immediately to Unicancer except for pregnancy discovered before the study patient has received any study drugs.

Given the lack of safety data from this association, a safety run-in of the 6 first patients recruited in the experimental arm was planned and revealed no unexpected or detrimental toxicities as such, trial was allowed to continue. Control of AEs related to the treatment are made by the sponsor and investigators from each participating center. Additionally, an Independent Data Monitoring Committee (IDMC), with expertise and experience in esophageal cancer, was set up to evaluate safety and tolerability at the end of the safety-run which observed no Dose Limiting Toxicity. The IDMC meet on regular basis (at least once a year). The second IDMC conducted in March 2022 has noticed that the global safety report for the 2 arms is acceptable with regard to risk/benefit balance initially expected.

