### Study objectives

The primary objective is to assess the efficacy of durvalumab, initially delivered in combination with FOLFOX and IMRT 50 Gy and then as maintenance therapy for treating patients with locally advanced esophageal cancer (adenocarcinoma or squamous cell carcinoma), in terms of centrally reviewed PFS (cPFS). As it is not a placebo-controlled study, an external anonymized blinded independent central review (BICR) of CT-scans (Response Evaluation Criteria in Solid Tumours RECIST v1.1) at baseline, M6, M9, M12, M18, and M24 is planned (see Fig. 1). Secondary objectives are PFS, overall survival, tolerance of the study treatments and quality of life.

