**Fig. 1 Fig1:**
[figure not shown]
Study design

Patients fulfilling the inclusion criteria are randomized between the two arms according to a 1:1 ratio using minimization method according to the following factors: *tumor stage, histology and center*.

➢ Arm A = experimental arm: durvalumab in combination with FOLFOX and definitive IMRT.Chemoradiotherapy (CRT): IMRT 50 Gy in 25 daily fractions in combination with FOLFOX regimen administrated during and after radiotherapy every two weeks for a total of 6 cycles. Durvalumab: 1500 mg one infusion q4w starting with CRT for a total of 12 cycles.➢ Arm B = standard arm: CRT: FOLFOX and definitive IMRT.Chemoradiotherapy IMRT 50 Gy in 25 daily fractions in combination with FOLFOX regimen administrated during and after radiotherapy every two weeks for a total of 6 cycles.

Given the lack of safety data from this association, a safety run-in of the 6 first patients was planned to assess for the absence of dose limiting toxicity (DLT).

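### SAE reporting ends at different times in the two arms and the AE rule gives arm B no end, so crude by-arm tolerance percentages would not be comparable

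*Protocol article*

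**What the plan says.** The section Treatment tolerance of the Protocol article holds several rules on how long safety events are reported.

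- **All AEs.** Recording starts at consent, and its end is given as "until 150 days after the last dose of durvalumab, whichever is longer, must be reported by the investigator". Only arm A receives durvalumab, and the sentence names no second date to compare with.
- **SAEs.** The investigator "notifies the UNICANCER pharmacovigilance unit of any SAE or any new event defined above, whether or not related to the research" during a trial reporting period that has three parts. It starts at consent. Its second part reads "Covers the entire period during which the patient is receiving the investigational treatment or is subject to specific procedures related to the trial". Its third part reads "Covers a period of 150 days after the last administration of durvalumab for Arm A and 30 days after FOLFOX for Arm B".
- **Later SAEs.** An SAE beyond 150 days that is judged related to the experimental treatment or to the research is reportable without a time limit. No separate threshold is given for arm B. Second cancers are also reportable without limit.

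Under Study objectives: "Secondary objectives are PFS, overall survival, tolerance of the study treatments and quality of life". Under Data management, qualitative variables are to be summarised by arm as counts and percentages. The article mentions no allowance for length of observation.

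**The concern.** Both arms receive the same 50 Gy radiotherapy and the same FOLFOX. Late effects of that treatment, and events from the disease itself, can occur in either arm. If they are recorded for much longer in arm A, a crude percentage of patients with an event will be higher there even if durvalumab adds nothing.

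Two things are at stake. The first is the tolerance comparison, a secondary objective and part of any risk/benefit judgement. The second is consistency between sites: eighteen centres must apply rules that do not say when arm B recording stops. Events that were never recorded cannot be recovered at analysis.

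**Working it through.** **Inputs.**
- Arm A schedule (Fig. 1 text): "Durvalumab: 1500 mg one infusion q4w starting with CRT for a total of 12 cycles". The cumulative dose under Medical procedures confirms the count: 12 × 1500 mg = 18,000 mg, as stated there.
- FOLFOX, both arms (Fig. 1 text): "administrated during and after radiotherapy every two weeks for a total of 6 cycles". Medical procedures has "FOLFOX 4 simplified protocol, 1 infusion every 2 weeks during 3 months starting with radiotherapy".
- Tails after treatment: 150 days (arm A) and 30 days (arm B).
- Radiotherapy lasts 5 weeks (Treatment planning).

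The article states no total window length, so there is no figure of its own to reproduce. Time runs from the first dose (day 0), with a month of 30.44 days.

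**Window lengths, third part of the SAE period.**
- Arm A, all infusions on time: 11 × 28 = 308 days to the last infusion; 308 + 150 = 458 days = 15.0 months.
- Arm B, all cycles on time: 5 × 14 = 70 days to the last cycle; 70 + 30 = 100 days = 3.3 months. If FOLFOX is taken to end at 3 months (91.3 days), the window is 121.3 days = 4.0 months.
- Ratio 458/100 = 4.6; gap 358 days = 11.8 months.
- Arm A after early stopping, 28 × (k − 1) + 150 days: k = 1 gives 150 days (4.9 months), k = 3 gives 206 (6.8), k = 6 gives 290 (9.5).

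So 15 months is a maximum, but even one infusion leaves arm A with a longer window than a fully treated arm B patient. In arm B the window closes 100 − 35 = 65 days, about 9 weeks, after radiotherapy ends.

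**Illustration of the effect on crude percentages.** Assume the same constant rate r per month in both arms, with every patient observed for the full window. The rates are not from the documents. Incidence = 1 − exp(−r × months), with 15.05 and 3.29 months:

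| r per month | Arm A | Arm B | Difference |
|---|---|---|---|
| 1% | 14.0% | 3.2% | 10.7 points |
| 2% | 26.0% | 6.4% | 19.6 points |
| 3% | 36.3% | 9.4% | 26.9 points |

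With only one infusion (4.93 months), arm A reads 4.8% at r = 1% and 13.7% at r = 3%, a difference of 1.6 to 4.4 points.

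**The rules set side by side.**
- The AE rule has an end for arm A and none for arm B.
- If scans to M24 (Study objectives) or the M12 plasma sample (Plasmatic biomarkers) count as trial procedures, the second part of the SAE period carries arm B far past 30 days, and the 30-day limit rarely bites. If they do not count, the difference between arms stands.
- The rule on later SAEs starts at 150 days. If the 30-day limit governs arm B, a related SAE between 30 and 150 days after FOLFOX is not clearly covered by either rule.

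**The case against.** A reader might infer that AEs in arm B are collected for only about 3 months and that the tolerance comparison is therefore biased by design. The article does not support that, for these reasons.

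- The 30-day limit belongs to SAE notification. The rule for recording all AEs is a different sentence, and it gives arm B no end at all.
- The parts of the SAE period are cumulative. The part on trial procedures may keep arm B under SAE reporting well past 30 days, with the 30 days serving as a minimum for patients who leave early.
- Serious late toxicity judged related to chemoradiotherapy can still be reported in arm B under the rule on later SAEs.
- About 10 of arm A's 15 months (308 days) are spent on durvalumab, where longer recording follows longer treatment. The post-treatment tails differ by 120 days (150 − 30).
- No formal between-arm safety test is described. A common-window or time-adjusted table may be in the analysis plan, which is not shown. The missing comparison date may have been lost in condensing the full protocol.
- The article does not say that the IDMC judged safety from crude percentages.

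All of this stands, and it limits the point. It does not remove it. Longer treatment with durvalumab does not justify counting shared chemoradiotherapy and disease events over different periods. An analysis plan can restrict or adjust a comparison but cannot supply arm B events that no rule required sites to record. Time adjustment alone is also imperfect when event rates change over time.

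**Conclusion.** The point holds as a should-fix. The text ends SAE notification at arm-specific times, leaves the AE window in arm B undefined, and contains rules that do not fit together. The window lengths follow from the stated schedules, assuming full on-time treatment and that the third part of the SAE period governs.

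The inflation of arm A is conditional: it arises if tolerance is compared as crude by-arm percentages over these windows. The 11 to 27 point range illustrates an upper case under assumed constant rates and complete observation; it is not an estimate for this trial, and early stopping or death would reduce it. The primary endpoint and its analysis are not touched.

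**What to change.** 1. Set one AE/SAE collection window for both arms, measured from randomisation and tied to an assessment already listed, for example M12 or M18. M15 matches no listed scan. M12 (365 days) falls about 57 days after a twelfth on-time infusion (365 − 308), so it would cut into arm A's 150-day tail; M18 would contain it. A common window for comparison need not shorten any longer follow-up in arm A.
2. Complete the AE sentence so that it gives an end date for arm B. State whether scans and samples count as trial procedures. Align the 150-day threshold for later SAEs with the arm B rule.
3. For patients already past their window, make the main between-arm tolerance table over the period common to both arms, to 30 days after the last FOLFOX. Show later events as observation-time-adjusted rates. First check how long sites actually recorded AEs in arm B.

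The cost is protocol wording, modest extra data entry for arm B and one extra table. The article reports 86 of 120 patients enrolled, so at that point 34 could still enter under the clarified rule.

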### Ancillary studies

#### Diagnosis biopsies

Anti-PD1/anti-PDL1 mAbs represent a major paradigm shift in cancer therapy. However, despite the unprecedented efficacy of these innovative treatments, determination of novel biomarker is of paramount interest. Currently, except PD-L1 expression only few parameters have been identified as predictive biomarkers of response of ICIs. In certain tumors subtypes such as esophageal carcinoma, expression PD-L1 Combined Positive Score (CPS) is associated with a higher response rate and survival to anti PD-1 in advanced/metastatic setting [5]. PD-L1 expression on carcinoma cells and stromal immune cells as well as characterization of Tumor Infiltrating Lymphocytes TILs/macrophages infiltrates will be correlated to disease free survival. Centralized review will be performed on formalin fixed paraffin embedded tumor block from diagnostic biopsies to determine an immunoscore. ([name], Pathology department CHU Toulouse).

#### Gut microbiota

Intestinal microbiota constitutes the largest accumulation of alien organisms (mainly bacteria) present on or in the human body [18]. Accumulating evidence indicates that the proper development of both intestinal and extra-intestinal components of the immune system requires the gut microbiota [19]. Anticancer immune response can be considered as a desirable form of autoimmunity that may be profoundly shaped by the microbiome. These may involve cross-reactivity between microbial and tumor antigens shaping T cell repertoires and/or microbial products stimulating pattern recognition receptors that influence the type and intensity of immune responses. It is of the utmost importance to understand how the microbiome in particularly the gut microflora, impacts natural cancer immunosurveillance in order to shape treatment-induced immune responses [20].

We hypothesized that in esophageal carcinoma as in many other solid tumors metagenomic signature would predict clinical response/resistance and/or immune-related adverse events. Stool samples from patients enrolled in the study are prospectively collected before the instauration of the treatment to perform metagenomic analyses in order identify metagenomics signatures that predict treatment response/resistance and immune-related toxicities.

